### Additional treatments

All patients will be treated according to a strictly standardized protocol that has been used in all our previous studies addressing traumatic memories and PTSD symptoms after CS [2,12,22]. The use of the sedative agent propofol will be avoided, however, because a previous animal study by our group has shown that this compound may facilitate memory consolidation under stress by interacting with the endocannabinoid system [23]. Likewise, the administration of stress doses of hydrocortisone will also be avoided as hydrocortisone may have a preventive effect on the development of PTSD symptoms after CS [24].

### Outcome measures

#### Primary endpoint

We intend to use stress symptom scores determined by the German version of the modified Post-Traumatic Stress Symptom 10 questionnaire (PTSS-10) at one year after CS as the primary endpoint. The PTSS-10 instrument has been repeatedly validated in patients after ICU treatment. In the first validation study performed by our group, we used a double-blind interview technique performed by psychiatrists, according to the Diagnostic and Statistical Manual of Mental Disorders (DSM), third edition criteria, to diagnose PTSD. This validation process demonstrated a high internal consistency (Cronbach’s α = 0.93) and a high test-retest reliability (intraclass correlation coefficient *r* = 0.89) of the instrument. The specificity and sensitivity for diagnosis of PTSD after ICU treatment at a cut-off value of 35 points of the questionnaire were 97.5% and 77%, respectively [25]. The second and more recent validation study was performed by an independent group and according to the newer DSM-IV criteria and demonstrated that a PTSS-10 score of >20 one week after weaning from mechanical ventilation reliably identified patients who were diagnosed with PTSD three months later: sensitivity 100%; specificity 76% with an area under the receiver-operating characteristic curve of 0.91 [26]. The questionnaire has been used in multiple studies investigating traumatic memories and post-traumatic stress after ICU treatment by our [2,25,27-30] and other [15,16,31-34] groups and has also been shown to be sensitive to a pharmacologic intervention aimed at reducing PTSD stress symptoms after CS and ICU therapy in general, namely the use of hydrocortisone [24,33]. When used in patients with coronary artery disease alone, without the stressor of recent CS and at a single time point, the instrument appears to considerably overestimate the incidence of full syndromal PTSD when compared with an interview technique (Structured Interview for DSM Disorders). But even when used under conditions for which the instrument has not been specifically validated, the PTSS-10 was able to adequately quantify the intensity of disease-related stress symptoms [34].

This instrument consists of two parts: *Part A* evaluates four standardized categories of traumatic memory from the ICU and *Part B* quantifies the presence and intensities of 10 PTSD-related symptoms [25]*.*

##### Traumatic memories

A category of traumatic memory as measured by *Part A* of the questionnaire is defined as the patient’s subjective recollection of nightmares, respiratory distress/dyspnea, feelings of anxiety/panic or pain. When completing the questionnaire, the patient is asked to answer each of these four items ‘yes’ or ‘no,’ independent of the number of occasions the adverse experience occurred. The number of ‘yeses’ answered by a patient is termed the number of traumatic memories. The intensity of traumatic memories is not specifically evaluated by the questionnaire.

##### PTSD-related chronic stress symptoms

The severity and presence of PTSD symptoms is quantified by *Part B* of the questionnaire and evaluates the presence and intensity of ten PTSD-related stress symptoms: sleep disturbance, nightmares, depression, hyperalertness, withdrawal (emotional numbing and inability to care for others), generalized irritability, frequent changes in mood, guilt, fear and avoidance reactions with regard to the ICU, and increased muscle tension. When evaluating these symptoms, the patients are asked to think back over the last few days (‘presently - that means in the past few days - I suffer from…’), and then asked if they had symptoms expressed by statements such as: ‘Jumpiness, I am easily frightened by sudden sounds or sudden movements’ (to evaluate hyperalertness), ‘fear of places and situations which remind me of the intensive care unit’ (to evaluate avoidance reactions), or ‘a bad conscience, blame myself, have guilt feelings’ (to evaluate guilt). Patients rated their symptoms using a scale from 1 (never) to 7 (always). A summary score can then be calculated that ranges from 10 to 70 points, with increasing scores indicating a higher prevalence and intensity of PTSD symptoms.

Traumatic memories and PTSS-10 stress symptom scores will be evaluated before surgery, one week after discharge from the ICU and at six months and one year follow-up time points (Figure 3).

#### Secondary endpoints

##### Traumatic memories

Traumatic memories will be quantified by *Part A* of the modified PTSS-10 instrument (see above).

##### PTSD symptom intensity as measured by the Post-Traumatic Stress Diagnostic Scale

The Post-Traumatic Stress Diagnostic Scale is a brief but reliable self-report measure of PTSD symptoms for use in both clinical and research settings. This instrument will be used as a confirmatory measure of stress symptom intensity [35].

##### Depression

We intend to use the German version of the Beck Depression Inventory, which is regarded as a standard instrument to evaluate depression in epidemiologic studies and to rate depression in patients with cardiovascular disorders. Depression will be quantified preoperatively as well as six months and one year after CS.

##### Delirium

Delirium is a common complication in patients undergoing CS and is associated with negative outcomes including cognitive decline, increased mortality and a higher of rate distress after ICU therapy, although the association with PTSD development is not entirely clear. The occurrence of delirium during ICU treatment will be monitored using the Confusion Assessment Method instrument, which is recommended as a standard tool for confusion assessment in the ICU (for time points see Figure 3).

##### Sedation/agitation

During ICU treatment, we intend to quantify the degree of sedation versus the occurrence of agitation by applying the widely used Richmond Sedation Agitation Score, which classifies the patients into three agitation categories: agitated, calm or sedated. The instrument will be administered every 8 hours while the patients are treated in the ICU (postoperative days 1 to 4).

##### Pain intensity

We will ask the patients to indicate how strong their current pain is by using a verbal rating scale where 0 = no pain and 10 = the worst pain imaginable. Pain intensity will be evaluated at every time point and every 8 hours during ICU treatment.

##### Degree of anxiety

We will ask the patients to indicate how strong their current anxiety is by using a verbal rating scale where 0 = no anxiety and 10 = the highest anxiety imaginable.

##### Health-related quality of life

Mental and physical quality of life including physical functioning will be evaluated using the German version of the self-administered 36-item Medical Outcomes Study Short Form Survey [36].

##### Endocannabinoids

By measuring plasma ECs (see Figure 3 for time points of these measurements), we want to show that homozygous carriers of the Bc*l*l *G SNP with enhanced GR sensitivity have lower EC signaling as a result of an increased inhibitory effect of glucocorticoids on the EC system and that this interaction can be influenced by the targeted behavioral intervention. This assumption results from a pilot trial that demonstrated increased circulating concentrations of ECs in CS patients with traumatic memories and PTSD symptoms [37], a larger study in individuals with PTSD from war and torture experiences [38] and decreased perioperative plasma levels of ECs in CS patients who developed depression after heart surgery [39]. Plasma concentrations of the ECs anandamide, 2-arachidonoylglycerol, palmitoylethanolamide, N-arachidonoyldopamine, arachidonoylglycine, oleoylethanolamide, stearoylethanolamide, 2-arachidonoylglycerolether, N-oleoyldopamine, docosatetraenoylethanolamide, dihomo-y-linoleoylethanolamide and virodhamine will be determined using a method based on high performance liquid chromatography-tandem mass spectrometry as previously described [39].

##### Cortisol

Morning plasma cortisol (8 am) will be determined using standard methods. Plasma cortisol will be measured because, in our previous study, homozygous carriers of the Bc*l*l SNP had significantly lower morning plasma cortisol levels [12]. Cortisol determination may allow us to study the effect of the intervention on plasma cortisol concentrations as a function of genotype. Low plasma concentrations of cortisol have been described in some but not all patients with PTSD and stress doses of cortisol may reduce the intensity of PTSD stress symptoms after CS [24].

### Genotyping and biochemical analysis

All analyses will be performed from venous blood collected in the appropriate tubes at the time points indicated in Figure 3.

#### DNA preparation and genotyping

At least one day before surgery and after informed consent by the patients, 10 ml of venous blood will be collected and genomic DNA will be extracted using the QIAamp DNA Blood Maxi Kit (Qiagen, Hilden, Germany). Information on the Bc*l*l polymorphic site of the GR was derived from the database of single nucleotide polymorphisms established by the National Center for Biotechnology Information [40]. Genotyping will be done by high-resolution melting DNA analysis with specific probe sets. High-resolution melting represents a simple and low-cost solution with a short turnaround time, which is important for the preoperative genotyping intended in our study. Genotype distributions will be checked for violations of Hardy-Weinberg equilibrium.

#### Biomarkers of the systemic inflammation

C-reactive protein and interleukin-6 (IL-6) will be measured because patients with PTSD are known to have a tendency for inflammation and a chronic inflammatory response may mediate the increased cardiovascular risk seen in these patients. C-reactive protein will be determined preoperatively and daily thereafter until ICU discharge. For reasons of cost containment, IL-6 measurements will be limited to three time points: preoperatively, postoperatively and one week after ICU discharge.

### Statistical analyses

#### Sample size calculations

In several previous studies in CS patients, we assessed post-traumatic stress using the PTSS-10 instrument that will also be the primary outcome measure in this study. Our preliminary work indicated an 8-point difference on the PTSS-10 scale between homozygous Bc*l*l *G carriers as opposed to non-carriers [12]. This study also showed that the PTSS-10 score did not significantly decrease until six months after surgery. We may assume that the non-trauma-focused control intervention does not change post-traumatic stress levels in homozygous patients and that the difference of 8 points in post-traumatic stress scores between non-carriers and homozygous individuals is clinically meaningful. This assumption is supported by the recent study discussed in the section *Primary endpoint*[26] that showed that even a relatively low PTSS-10 score (>20) in patients one week after ICU therapy and weaning from mechanical ventilation was highly predictive for the later development of PTSD. Based on the results of our pilot study [12], we make the following assumptions: first, the mean PTSS-10 score one year after ICU discharge is 18±8 (mean ±SD) for non-Bc*l*l *G carriers and heterozygous Bc*l*l *G carriers and 25±8 for homozygous Bc*l*l *G carriers each under control intervention. Second, the mean PTSS-10 score one year after ICU discharge is 18 ±8 for all patients under experimental intervention. Both assumptions show a quantitative intervention-SNP interaction. An overall sample size of 252 patients (84 per SNP group) is needed assuming a type I error rate of 5% and a type II error rate of 80% to detect a statistically significant differential treatment effect between the genotype groups. The sample size calculation was performed by Nquery (Statistical Solutions Ltd.,[name]). Further, experience from former studies shows a perioperative mortality of 8% and a loss to follow-up of approximately 20% of patients at the six-month time point [2,12]. Adjustment for a drop-out rate of 30% leads to a total of 120 required patients (120–0.3 × 120 = 84) per SNP group. In our previous study in 126 Western European CS patients from our institution, 43% were non-carriers of the Bc*l*l *G, 43% were heterozygous Bc*l*l *G carriers and 14% were homozygous [12]. This means that we will have to genetically screen approximately 872 patients to detect 120 homozygous individuals eligible for randomization. Genetic screening will also result in the identification of approximately 376 non-carriers and 376 heterozygous individuals. These patients will also be randomly allocated to the control and the targeted intervention group but, to reduce costs, only 120 individuals with each genotype will be randomly selected by choosing every third consecutive heterozygous or non-carrier patient included in the study. Thus, we will have to screen and genotype 872 patients to include 360 patients into the final analyses (Figure 4).

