## Abstract

**Background:**

Cardiac surgery is one of the most commonly performed surgical procedures worldwide with >700,000 surgeries in 2006 in the US alone. Cardiac surgery results in a considerable exposure to physical and emotional stress; stress-related disorders such as depression or post-traumatic stress disorder are the most common adverse outcomes of cardiac surgery, seen in up to 20% of patients. Using information from a genome-wide association study to characterize genetic effects on emotional memory, we recently identified a single nucleotide polymorphism of the glucocorticoid receptor gene (the Bc*l*l single nucleotide polymorphism) as a significant genetic risk factor for traumatic memories from cardiac surgery and symptoms of post-traumaticstress disorder. The Bc*l*l high-risk genotype (Bc*l*l GG) has a prevalence of 16.6% in patients undergoing cardiac surgery and is associated with increased glucocorticoid receptor signaling under stress. Concomitant animal experiments have confirmed an essential role of glucocorticoid receptor activation for traumatic memory formation during stressful experiences. Early cognitive behavioral intervention has been shown to prevent stress-related disorders after heart surgery.

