### The Bc*l*l SNP of the glucocorticoid receptor influences traumatic memories and PTSD stress symptoms in patients undergoing cardiac surgery

The major risk factor for PTSD development in critically ill patients is the presence of traumatic memories from highly stressful experiences during ICU treatment [2,8]. Animal experiments performed by our research group and others have repeatedly shown that the encoding of traumatic experiences into emotional memory during stress is facilitated by a stress-induced increase in glucocorticoid [9] and endocannabinoid signaling [10]. Using information from a genome-wide association study to characterize genetic effects on emotional memory in volunteers (Figure 1), we have recently identified an intronic SNP of the glucocorticoid receptor (GR) gene (the Bc*l*l SNP) in patients undergoing CS that is associated with increased cortisol sensitivity of the GR and, thus, enhanced glucocorticoid signaling under stress. The increased cortisol sensitivity is seen in homozygous carriers of the Bc*l*l *G allele, which has a prevalence of 14% in the western European population [11] and 16.6% in our patients undergoing CS [12]. Homozygous carriers had a significantly increased risk for traumatic memories and PTSD symptoms of chronic anxiety, pain, depression and impaired health-related quality of life after CS [12]. We very recently confirmed this finding in a second study in an independent group of patients having CS (unpublished, Figure 2). In combination, these well-corroborated findings allow the preoperative identification of patients at risk for PTSD symptoms after heart surgery who could benefit from preventive interventions.

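### One pilot study is given two homozygous prevalences, 16.6% and 14%; the 872 to be screened fits only 14%, and at 16.6% the every-third rule secures 120 per genotype only under one reading of when screening ends

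*Protocol article*

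**What the plan says.** In the Background, the section on the Bcll SNP says that homozygosity for the G allele "has a prevalence of 14% in the western European population [11] and 16.6% in our patients undergoing CS [12"]. The two figures are kept apart: 14% belongs to a general-population source, and 16.6% to the group's own cardiac surgery patients (reference 12). The Abstract repeats the second figure: the high-risk genotype "has a prevalence of 16.6% in patients undergoing cardiac surgery".

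Sample size calculations cites reference 12 again, with a different value. "In our previous study in 126 Western European CS patients from our institution", it reports, 43% were non-carriers, 43% were heterozygous and "14% were homozygous". It concludes that "we will have to genetically screen approximately 872 patients to detect 120 homozygous individuals eligible for randomization", with about 376 non-carriers and 376 heterozygotes found along the way. To save cost, 120 of each low-risk genotype are to be taken by choosing every third consecutive patient. The section closes by giving 872 as the total to screen and genotype in order to include 360.

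**The concern.** One source carries two prevalences for the quantity that drives recruitment. The Abstract also conflicts with itself: it states 16.6%, yet expects 120 GG patients from 872 genotyped, and 16.6% of 872 is about 145.

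Two things depend on the figure. The first is the amount of consent, blood sampling and preoperative genotyping, which differs by about 150 patients between the two values. The second is the low-risk selection. The plan fixes both a target (120 per genotype) and a sampling fraction (one in three), and these agree only over a limited range of prevalence. The plan does not say whether screening ends at 872 patients or at 120 GG. At 14% the two nearly coincide; at 16.6% they do not.

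**Working it through.** **Inputs**, all from Sample size calculations unless noted: 120 per genotype, from 84 evaluable and 30% drop-out; GG prevalence 14%; GG prevalence 16.6% (Abstract and Background); 872 screened; sampling fraction 1/3; PTSS-10 difference of 7 points (25 against 18), SD 8, two-sided 5%.

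**Assumption.** No low-risk split is given to go with 16.6%. An equal split is used, as in the plan's own 43/43.

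**Reproducing the plan's figure**
- 84/(1 − 0.30) = 120.
- 120/0.14 = 857.1, against 872 stated (less than 2% apart).
- 376 + 376 + 120 = 872, which is 43.1%, 43.1% and 13.8%. These round to the stated 43/43/14.
- Any prevalence that rounds to 14% (13.5% to 14.5%) gives 120/0.145 = 828 to 120/0.135 = 889. The 872 lies inside that range.

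**The two prevalences side by side**

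| Quantity | GG 14% | GG 16.6% |
|---|---|---|
| Screened to find 120 GG (120/p) | 857 | 723 |
| *Stop at 120 GG:* low-risk per genotype, (N − 120)/2 | 369 | 301 |
| Every third of these | 123 | 100 |
| *Screen all 872:* GG found | 122 | 145 |
| Low-risk per genotype | 375 | 364 |
| Every third of these | 125 | 121 |

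**Where the rule breaks even, if screening stops at 120 GG.** Taking 120 of each low-risk genotype at one in three needs 120 × 3 × 2 = 720 low-risk patients, so 840 in all, and 120/840 = 14.3%. Above that prevalence the rule falls short. At 16.6% the fraction needed is 120/301 = 0.40, not 0.33.

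**Consequence at 16.6%, stopping at 120 GG.** Enrolled: 120 + 2 × 100.5 = 321 instead of 360. Evaluable per low-risk genotype: 100 × 0.7 = 70 instead of 84, or 35 per arm instead of 42.
- Pairwise contrast of treatment effects, planned: SE = 8 × √(2/42 + 2/42) = 2.47; 7/2.47 − 1.96 = 0.87; power 81%.
- Pairwise contrast, reduced: SE = 8 × √(2/42 + 2/35) = 2.59; 7/2.59 − 1.96 = 0.74; power 77%.
- First-step interaction test (2 df): about 84% with 84/84/84 evaluable and about 81% with 84/70/70.

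**Sensitivity to the split.** If Hardy-Weinberg proportions held at 16.6% (48.3% heterozygous, 35.1% non-carriers), every third of 872 would give 872 × 0.351/3 = 102 non-carriers and 872 × 0.483/3 = 140 heterozygotes. Non-carriers would then be short even with all 872 screened. This is an assumption and departs from the plan's 43/43.

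**Can the documents settle the prevalence?** 126 × 0.166 = 20.9 and 126 × 0.14 = 17.6. Whole counts of 21 (16.7%) and 18 (14.3%) lie close to the two figures, so neither can be ruled out. No genotype counts for the whole pilot sample are given.

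**The case against.** The best defence is that Sample size calculations is consistent within itself: it uses one prevalence, and 872 follows from it within rounding. A reader might infer that 872 is an arithmetic error because it equals neither 857 nor 723. The text does not support that, since the figure is given as approximate and the split behind it rounds to 43/43/14.

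A reader might also infer that the low-risk groups will fall short at 16.6%. The plan nowhere says that screening stops at 120 GG, and both the Abstract and the end of Sample size calculations present 872 as the number to be genotyped. On that reading the rule gives about 121 each, and the shortfall does not arise under an equal split.

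Further, if 14% is the wrong figure, the error protects the scarce group: the chance of at least 120 GG among 872 is about 0.99 at 16.6%, against about 0.60 at 14%. The power loss is small, and the first-step test stays above 80% even in the unfavourable case. Finally, the two percentages might describe different subsets of the pilot, although the text does not say so.

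All of this limits the point, but part of it remains. The same reference still carries two values. The Abstract's 16.6% still does not give 120 GG from 872. Screening all 872 at 16.6% leaves about 25 GG patients above target with no stated rule for them, and a margin of about one patient per low-risk genotype.

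**Conclusion.** The point holds as an internal contradiction with a conditional consequence. GG prevalence in the pilot is 16.6% in one place and 14% in another, and the documents do not show which is right. The 872 is sound for 14%. At 16.6% it exceeds the number needed for 120 GG by 872 − 723 = 149 patients (17%).

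The one-in-three rule delivers 120 per low-risk genotype with some margin near 14%. At 16.6% the result depends on an unstated stopping point: about 100 each if screening ends at 120 GG, or about 121 each, with about 145 GG, if all 872 are screened. In the first case the cost is about 4 points of power for the pairwise contrast and about 3 for the interaction test. These figures rest on an equal low-risk split, 30% drop-out, a 7-point difference and an SD of 8. The effect is modest, but it bears on the design's headline numbers and is cheap to remove.

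**What to change.** 1. Check the genotype counts in the pilot study. State one GG prevalence with its source, and use it in the Abstract, the Background and Sample size calculations. If the two figures refer to different subsets, say so and say which one governs planning.
2. Restate the screening number to match: about 857 at 14%, or 723 at 16.6%. Do not lower it until the counts are confirmed, because 723 would be too few for 120 GG if 14% is right.
3. State whether screening ends at 872 patients or at 120 GG. If it ends at 872, say what happens to GG patients beyond 120.
4. Replace the fixed one-in-three rule with random low-risk selection tied to GG accrual, for example one non-carrier and one heterozygote for each GG patient enrolled. This holds 120 per genotype at either prevalence: about 301 of each low-risk genotype would be available at 16.6% and about 369 at 14%, under an equal split.

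The cost is a check of existing data, some wording and a selection rule in the enrolment tool. No patients are added, and if 16.6% is confirmed about 149 fewer need genotyping.
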